## Abstract

*Background*. Meditation practices are associated with a reduction in adrenergic activity that may benefit patients with severe cardiac arrhythmias. This paper describes the design and methods of a pilot study testing the feasibility of a phone-delivered mindfulness-based intervention (MBI) for treatment of anxiety in patients with implantable cardioverter defibrillators (ICDs). *Design and Methods*. Consecutive, clinically stable outpatients (*n* = 52) will be screened for study eligibility within a month of an ICD-related procedure or ICD shock and will be randomly assigned to MBI or to usual care. MBI patients will receive eight weekly individual phone sessions based on two mindfulness practices (awareness of breath and body scan) plus home practice with a CD for 20 minutes daily. Patients assigned to usual care will be offered the standard care planned by the hospital. Assessments will occur at baseline and at the completion of the intervention (between 9 and 12 weeks after randomization). The primary study outcome is feasibility; secondary outcomes include anxiety, mindfulness, and number of administered shocks during the intervention period. *Conclusions*. If proven feasible and effective, phone-delivered mindfulness-based interventions could improve psychological distress in ICD outpatients with serious cardiovascular conditions.

## 1. Introduction

Sound evidence supports the value of meditation-based interventions in patients with cardiovascular disease. As far back as 1971, Wallace et al. [1] described the physiological characteristics of the “relaxation response” associated with meditative practices. These included a general decrease in sympathetic nervous system (SNS) activity, oxygen consumption, and blood lactate levels. Later studies comparing subjects practicing meditation with nonpractitioners found reduced endorgan sensitivity to catecholamines, possibly mediated by a lower percentage of functional lymphocyte beta-adrenergic receptors [2]. This overall reduction in the SNS activity may be beneficial in patients affected by cardiovascular disease as suggested by a number of studies of transcendental meditation [3–8]. Fewer studies, however, have explored the possible effect of mindfulness meditation interventions in this population [9–11].

The most widely available mindfulness training course is the mindfulness-based stress reduction (MBSR) program [12] created in the early eighties by Jon Kabat-Zinn. MBSR offers training in traditional mindfulness meditation adapted to a non-Buddhist, clinical context. While MBSR has shown positive results in a wide range of medical and psychological conditions, including anxiety and depression [13, 14] some features of the program, such as the need to attend eight weekly classes and the recommended duration of daily home mindfulness practice (usually 45 minutes), may constitute a barrier to participation for patients with severe chronic cardiovascular disease.

With this study, we sought to evaluate whether a new delivery method (phone delivery) would overcome some of the above-mentioned barriers to mindfulness training in patients with implantable cardioverter defibrillators (ICDs). This is a population with severe underlying cardiac conditions and considerable prevalence of psychological distress, with figures reaching up to 38% for clinically significant anxiety and depression [15, 16] for which mindfulness training may be beneficial. We describe here the design and methods of a pilot randomized clinical trial examining the feasibility of a mindfulness-based, phone-delivered intervention in a group of ICD patients. Secondary outcomes will include the preliminary estimation of efficacy of the intervention on anxiety and mindfulness scores.

## 2. Design and Methods

The “Coping with ICD study” (Clinicaltrials.gov NCT01035294) is a pilot randomized clinical trial designed to evaluate the feasibility of a phone-administered, mindfulness-based training program for the treatment of psychological distress in patients undergoing an ICD procedure, or reporting an ICD-related event (shocks).

### 2.1. Setting

The study will be conducted at the university campus of the UMass Memorial Medical Center (UMMMC), a tertiary care medical center located in Worcester, MA admitting more than 300 patients every year for ICD procedures.

### 2.2. Recruitment and Screening Procedures

Patients scheduled for an ICD-related procedure or who recently had an ICD-related event (shocks) will be screened for study eligibility within a month of the procedure/event. All potentially eligible patients will receive a letter inviting them to participate and asking them to call a dedicated phone number to communicate their possible interest. To ensure an unbiased presentation of the study, we developed a script of the first phone contact call. If the patient expresses interest, a screening visit will be scheduled.

Patients will be eligible if they meet the following criteria: age ≥21, ICD-related procedure or recent ICD shocks, ability to understand and speak English, and access to a telephone. Patients will be excluded from the study under the following conditions: inability/unwillingness to give informed consent, cognitive impairment, New York Heart Association (NYHA) functional class >III or Canadian Cardiovascular Society (CCS) angina class III or IV or otherwise clinically unstable, pending coronary bypass or heart transplantation, comorbid life threatening conditions, and ongoing severe depression or psychosis. The Blessed Orientation Memory and Concentration test [17] will be used to screen patients for cognitive impairment. Patients scoring ≥10 will be excluded from the study since mindfulness training requires a normal cognitive function and ability to focus the attention; cognitive impairment would limit the ability of the subjects to adequately participate in the intervention. Screening for ongoing depression and psychosis will be based on DSM criteria of major depressive disorder or psychosis as documented by the physician in the most recent medical evaluation. Once eligibility is confirmed, we will obtain informed consent in person. Since the study requires access to protected health information (PHI), a HIPAA authorization will be signed by each study subject in order to access his or her medical records. After baseline data collection is completed, participants will be randomly assigned to the intervention or to the control group.

### 2.3. Randomization

 The randomization sequence will be generated using STATA [18] “ralloc” command, which produces a sequence of group assignments randomly permuted in blocks of several sizes. Block sizes of 4 and 6 will be used in this study. A programmer will generate the random allocation sequence and upload the table containing the random sequence of group assignments to an Access database. Based on this table, the participant will be automatically assigned to a group by clicking the “Randomize” button. 

### 2.4. Follow-Up

 To maximize retention, patients in both study arms will receive a weekly phone call inquiring as to whether they had questions regarding their participation. When a participant misses an intervention session, he/she will be immediately contacted. After three missed contacts, nonresponders will be sent a letter encouraging them to discuss their status. Participants will not be expected to stop any of their usual support services, for example, professional counseling, support groups, or any antianxiety or antidepressant treatment.

The study protocol and the study materials were approved by the Committee for the Protection of Human Subjects at the University of Massachusetts Medical School (Docket H-13078).

### 2.5. Mindfulness-Based Intervention (MBI)

#### 2.5.1. Rationale

The study intervention will adapt elements of the MBSR [12] program (whose standard curriculum includes participation in eight weekly classes, lasting two and a half hours; an all-day retreat; practicing mindfulness and yoga exercises at home for 45 minutes/day) to the needs of patients with ICDs. Changes will include in person phone delivery versus in class delivery of the intervention; shortening of the duration of the training sessions and of the individual home practice; the exclusion of the all-day retreat and of yoga exercises.

Several conditions suggested the need for a modification of the standard MBSR program for ICD patients. (1) Driving is usually discouraged in ICD patients during the months immediately following ICD surgery [19] since up to 8% of patients experience a shock while driving [20]. This circumstance would limit attendance at regular MBSR classes. (2) Psychological distress is higher soon after ICD implantation [15], and it is important to start the intervention as close as possible to the ICD procedure to help alleviate symptoms when they are more intense. Since most MBSR programs are usually offered at discrete times, it may not be possible for many ICD patients to receive the intervention when it is most needed. (3) Physical activity may trigger arrhythmias and shocks [21], and it is often avoided by patients at this early stage for fear of ICD discharges. (4) The clinical condition of this population with severe underlying cardiovascular disease may limit their ability to attend classes and to practice mindfulness exercises for longer periods.

#### 2.5.2. Intervention Content

The conceptual background informing the intervention was guided by the “parsimonious” model recently proposed by Carmody [22]. Briefly, in this model mindfulness interventions are described as training in self-regulation of attention and recognition of the sensations, cognitions, and feelings that comprise daily experience. In the untrained individual, negative cycles of associated thoughts, sensations, and feelings are maintained by attention being absorbed in their content and/or meaning. For example, the presentation of a frightening thought generates an associational cycle in which the thought leads to unpleasant sensations of constriction. This negative cycle can begin with a thought, a feeling, or a sensation and is then self-maintained as long as the subject's attention remains engaged with the content of any of its components. In the process of mindfulness training, the subject learns to *notice* which component the attention is directed toward in any given moment and to *choose *to keep the attention where it is or to redirect it to another object, usually an arousal “neutral” object such as the sensations of breathing.

Consistently with our endeavor of adapting elements of the MBSR curriculum to meet the needs of ICD patients, the intervention's content will be simplified to include two basic components: (1) the body scan, a technique based on the cultivation of attention to bodily sensations and cognitions that would normally go unnoticed and (2) training in the awareness of the sensations of breathing. In addition, participants will be gradually taught to direct their attention to simple activities of daily life (such as eating and drinking), to sounds, visual objects, thoughts, and emotions and to recognize when their attention is no longer focused on that specific object of attention. At the final session, participants will practice “open awareness” in which they will be instructed to just notice which events (physical sensation, sound, visual object, and/or thought) their attention will be spontaneously drawn to from moment to moment. Patients will not receive additional materials usually provided to MBSR trainees in the form of poetry or other readings. In addition, lovingkindness (“metta” practice—a technique based on deliberately generating feelings of compassion, benevolence, and acceptance towards self and others) will not be a component of the study intervention. This technique was excluded because there is insufficient evidence for a benefit of such a practice on psychological well-being in patients with cardiovascular disease and because it would imply a different study hypothesis that deserves to be tested in a separate investigation.

#### 2.5.3. Intervention Format

 The study intervention will consist of eight phone-delivered, individual training sessions each lasting 30 minutes (Table 1). Twenty minutes will be spent on intervention delivery, and 10 minutes on questions, answers, and scheduling the next intervention. At the beginning of the study patients will receive an audio CD consisting of two different mindfulness practices, each lasting about 20 minutes, consistent with the techniques learned during each session with the instructor: track 1: sitting practice; track 2: body scan practice. After the delivery of the first intervention, participants will be encouraged to listen to the audio CD every day, at least once a day, and then throughout the study. The CD can be played using a regular CD player or a computer, and a portable CD player will be given to participants when needed.

To ensure that the delivery of the intervention will be similar across instructors we developed a script of each session. Although instructors will not have to follow the script verbatim, they will be expected to follow the sequence indicated in the script.  Figure 1 shows the components of the intervention, each in a different color, and the session at which it was introduced. By looking at each row in this table it is possible to identify the content of each individual session.

### 2.6. Instructors

The instructors will be healthcare professionals and graduates of the Center for Mindfulness Professional Training Program with at least five-year experience in mindfulness training and a personal mindfulness practice. Prior to the study beginning, they will receive three hours of training, including a detailed review of the intervention script. We will hold bimonthly meetings to discuss any questions or difficulties that might be arising during the intervention sessions. Each patient will be trained by the same instructor throughout the intervention, and although not blinded to group assignment, instructors will be blinded to the study outcomes. At the end of each session, the instructors will complete an attendance form and a checklist in which duration and delivery of the intervention as specified in the intervention script as well as their perception of the patient's level of engagement during the session will be recorded. Patient's engagement will be evaluated immediately after each session and scored on a scale of 1 (completely unengaged) to 10 (extremely engaged). In order to monitor the provider's adherence to the protocol and the consistency of the delivery of the intervention across providers, each session will be digitally recorded by the instructor. Electronic copies of the attendance form, the checklist, and the MP3 file of the recorded session will be emailed weekly to the study manager.

### 2.7. Control Group: Usual Care (UC)

 Patients in the control group will receive the usual care provided by UMMMC to all ICD patients. Due to budgetary constraints, it was not possible to use an active control condition. To offset this limitation at least partially, patients in the usual care arm will receive a weekly phone call (duration: 5–10 minutes) that, although not designed to offer a specific intervention, will be aimed at addressing patients' possible concerns regarding their health or the ICD. If such concerns presented, the patient will be advised to contact his/her physician or nurse at the electrophysiology clinic. This phone call will also help to equalize the amount of study contact between study arms.

### 2.8. Study Assessments

Data collection will be performed at the baseline interview immediately after consent is provided, and nine weeks after enrollment once the intervention is completed.

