#### 2.8.2. Secondary Outcomes

MindfulnessBaseline and postintervention mindfulness scores will be measured using the Five Facets of Mindfulness (FFM) questionnaire [25], an instrument derived from a factor analysis of questionnaires measuring mindfulness in daily life. It consists of 39 items, exploring different aspects of mindfulness: observing, describing, acting with awareness, nonjudging of inner experience, and nonreactivity to inner experience. Each item is rated on a Likert scale ranging from 1 (never or very rarely true) to 5 (very often or always true). The FFM has shown good internal consistency [25].

Anxiety Anxiety will be measured using the Hospital Anxiety and Depression Scale, [26] a 14-item self-administered questionnaire with two subscales measuring anxiety and depression, with higher scores indicating greater psychological morbidity. A cutoff point of 8 is usually recommended to screen patients for clinically significant depression and anxiety [26–28]. A correlation between 0.6 and 0.8 has been reported between the HADS and other commonly used questionnaires for anxiety and depression such as the Beck Depression Inventory and the State-Trait Anxiety Inventory [27], and its validity has been confirmed both in hospital settings and primary care medical practice [29]. Furthermore, the HADS offers the advantage of focusing on cognitive symptoms of anxiety instead of physical symptoms; this is particularly useful in cardiac patients where symptoms of the underlying cardiac disease may be similar or identical to those resulting from somatic manifestations of anxiety.

Number of ShocksThe number of delivered shocks (if any) will be abstracted from the electronic version of the follow-up visit 9 weeks after enrollment. While patients can receive care in other centers during the follow-up period, ICD-specific follow-up visits are mostly performed at UMMMC, thus limiting the chance of missing important information about ICD functioning and arrhythmic events.

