### 2.9. Data Sources

 Demographic data, physical activity, use of other complementary/alternative therapies, anxiety, and mindfulness scores will be obtained from self-administered standardized questionnaires. Medical history, including past history of anxiety or depression, prescription of psychotropic medications and antiarrhythmic drugs, indication for ICD implantation, functional class, and number of shocks/arrhythmic episodes and hospital readmissions will be abstracted directly from the medical record. Study questionnaires will be administered by in-person interview at baseline and by phone interview at week 9. Questionnaires delivery via phone interview (following intervention) was preferred to mailing of questionnaires because response rates tend to be higher using the telephone as compared with mailed surveys [30]. Furthermore, the study population will likely include older individuals who may have difficulties reading the surveys. There is evidence that for some people, particularly those of low literacy and education, telephone interview is less intimidating.

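### The single post-baseline assessment is timed in conflicting ways (at completion, 9 to 12 weeks after randomisation, or week 9), and one of these rules depends on an event that only the MBI arm has

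*Protocol article*

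**What the plan says.** Four places in the protocol article time the one assessment after baseline.

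- Abstract: "Assessments will occur at baseline and at the completion of the intervention (between 9 and 12 weeks after randomization". The origin is randomisation, the window is three weeks wide, and the trigger is completion.
- Section 2.8: "nine weeks after enrollment once the intervention is completed". The origin is enrolment, no window is given, and completion is mentioned.
- Section 2.8.2, Number of Shocks: the count is "abstracted from the electronic version of the follow-up visit 9 weeks after enrollment". The origin is enrolment, and completion is not mentioned.
- Section 2.9: questionnaires are given "by in-person interview at baseline and by phone interview at week 9". No origin, window or completion condition is stated.

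The abstract also describes the shock outcome as the "number of administered shocks during the intervention period", a period that is not defined for usual care.

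The MBI course is eight weekly phone sessions (abstract; Section 2.5.3). Section 2.4 foresees missed sessions and has the patient contacted, but does not say whether the assessment then moves. Usual-care patients receive a weekly call (Section 2.7) with no stated number or end. Section 2.5.1 says "Psychological distress is higher soon after ICD implantation". Table 2 assumes a mean HADS anxiety change of 3.0 under usual care and 5.1 under MBI.

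**The concern.** Completing the intervention is an event in one arm only. Eight weekly sessions leave about one week of slack before week 9. If the abstract's rule is followed, MBI patients who finish late would be interviewed after week 9, and nothing says that usual-care interviews would move with them.

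This matters because anxiety is expected to fall without the intervention. Section 2.5.1 says that distress is greater early on, and Table 2 gives usual care a 3.0-point change. Table 2 shows no sign, so reading it as a fall is an interpretation, though the natural one. If MBI patients are measured later on a falling curve, some natural recovery is credited to MBI.

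The regression in Section 2.11 shows treatment, age, gender and baseline score. No term for assessment time is visible, although the formula ends in an ellipsis. Such a term would not be a reliable repair: where timing depends on arm and attendance, adjusting for it is entangled with the treatment effect.

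Anxiety is a secondary outcome, but it is the one on which the sample size rests (Section 2.12), and Sections 1 and 2.11 make its effect estimate a stated aim.

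**Working it through.** **Inputs.** From Table 2: change 3.0 (SD 2.2) in control and 5.1 (SD 2.6) in intervention, difference 2.1, two-sided alpha 0.05, power 0.80, total 42. From Section 2.12: 52 enrolled, 20% loss. From the abstract and Section 2.8: week 9 against at most week 12, so the largest gap is 12 − 9 = 3 weeks.

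**The plan's own figure.** Pooled SD = √((2.2² + 2.6²)/2) = 2.408. The normal-approximation formula for a difference of 2.1 gives 21 per arm, 42 in total, as stated. 52 × 0.8 = 41.6, which agrees with 42 after rounding. With 21 per arm, SE = 2.408 × √(2/21) = 0.743 on 40 degrees of freedom.

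**Bias from a timing gap.** Let g be the mean number of weeks by which MBI is assessed later than usual care. The documents do not give g, nor the course of anxiety after week 9, so two assumed shapes are shown. Both take the 3.0-point fall as reached at week 9, which is itself an assumption.

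- Linear: 3.0/9 = 0.33 points per week, so bias = 0.33 × g.
- Slowing (exponential, half-life h weeks): total fall P = 3.0/(1 − 2^(−9/h)), and bias = P × (2^(−9/h) − 2^(−(9+g)/h)). For g = 3 and h = 3, P = 3.43 and bias = 3.43 × (0.125 − 0.0625) = 0.21. For g = 3 and h = 9, P = 6.0 and bias = 6.0 × (0.500 − 0.397) = 0.62.

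The false-positive rate is the chance that a two-sided 5% t-test with 21 per arm rejects when MBI has no effect and the true difference in means equals the bias (noncentral t, noncentrality = bias/0.743).

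| Mean gap | Linear: bias (share of 2.1) | Linear: false-positive rate | Slowing, h = 3 to 9: bias (share of 2.1) | Slowing: false-positive rate |
|---|---|---|---|---|
| 0 weeks | 0 | 5% | 0 | 5% |
| 1 week | 0.33 (16%) | 7.2% | 0.09 to 0.22 (4% to 11%) | 5.2% to 6.0% |
| 2 weeks | 0.67 (32%) | 14.1% | 0.16 to 0.43 (8% to 20%) | 5.5% to 8.7% |
| 3 weeks | 1.00 (48%) | 25.9% | 0.21 to 0.62 (10% to 29%) | 5.9% to 12.8% |

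The test is an unadjusted comparison of changes, matching the basis of Table 2 rather than the Section 2.11 regression. No corresponding size can be given for mindfulness scores, because the article gives no usual-care change for them.

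**The case against.** The strongest reply is that unequal timing is an inference. The abstract gives one window without separating the arms, and the body gives week 9, also without separating them. Section 2.8 can be read as plain description: eight weekly sessions are over by week 9. On that reading both arms are measured together and no bias arises. This stands: the wording permits a gap but does not create one.

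Three stronger readings are tempting and should not be drawn.

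- *That MBI patients will drift to week 12 while usual care stays at week 9.* No section says so, and none says that missed sessions are rebooked.
- *That patients who do not complete the course are left out of the assessment.* Sections 2.8.2 and 2.9 give week 9 with no completion condition. Section 2.8.1 treats sessions attended as an adherence measure and counts dropout separately, so partial attendance is expected.
- *That MBI has up to 12/9 = 1.33 times the exposure for shocks.* Section 2.8.2 takes the count from the week 9 visit in both arms. The ratio arises only if that definition is set aside for the abstract's looser phrase, and longer exposure would count against MBI.

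The size is also open to challenge, fairly. The full 3-week figure needs a mean gap of 3 weeks, so essentially every MBI patient at week 12 and every control at week 9. The statement in Section 2.5.1 fits an early fall that slows better than a straight line. The 3.0 is a hypothetical value from two studies whose follow-up length is not given, and patients may enter up to a month after a procedure or shock, so individual courses will differ.

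What the reply does not remove is the contradiction. The article states the timing several times and the statements disagree, so this is not detail left to a fuller document.

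**Conclusion.** The contradiction is real and should be resolved. It concerns both the window (week 9 or weeks 9 to 12) and the origin (enrolment or randomisation). One version ties the assessment to an event that only the MBI arm has.

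The consequence is conditional. With everyone assessed at week 9, the bias is zero. The 1.0-point, 48% and 26% figures are a ceiling that needs both a full 3-week mean gap and an assumed linear fall continuing past week 9. With an assumed slowing decline, the same gap gives 10% to 29% of the planned effect and a false-positive rate of about 6% to 13%. If only some MBI patients run late, the mean gap and the bias are smaller still.

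The exposure is confined to secondary estimates, anxiety above all and mindfulness if it too changes over time. The feasibility metrics that form the primary outcome do not depend on the date of the HADS interview. In a pilot, the damage would be a misleading preliminary effect size. The point is worth acting on because the correction is nearly free before data collection and the bias is hard to remove afterwards.

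**What to change.** Reconcile the abstract and Sections 2.8, 2.8.2 and 2.9 to one rule:

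- one assessment time counted from randomisation, with the same window in both arms;
- HADS and FFM attempted at that time in every randomised patient, whatever the session attendance;
- shocks counted from randomisation to that same date in both arms, replacing the reference to the intervention period. No exposure offset is then needed on account of differing assessment dates.

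The sample size does not change: with a common time the timing bias is zero and 42 analysable patients stands. The cost is a wording change and a small practical trade-off. If week 9 is kept, some MBI patients may be assessed before their last session. If a later week is chosen, usual-care interviews move later, by up to three weeks if week 12 is used.
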